### Interim analyses {21b}

This is not applicable. There are no interim analyses planned.

### Methods for additional analyses (e.g., subgroup analyses) {20b}

This is not applicable. There are no subgroup analyses planned.

### Methods in analysis to handle protocol non-adherence and any statistical methods to handle missing data {20c}

As mentioned above, missing or incomplete data will be considered in the intention-to-treat analysis using the maximum likelihood estimation method.

### Plans to give access to the full protocol, participant-level data and statistical code {31c}

Once the study has been completed and the results published, the corresponding author will provide access to the coded data upon reasonable request.

## Oversight and monitoring

### Composition of the coordinating center and trial steering committee {5d}

The principal investigator and the members of the research team are responsible for monitoring the development of the research.

### Composition of the data monitoring committee, its role, and reporting structure {21a}

Considering the characteristics of this trial (the short duration of the interventions and no expected estimated risks for participants), a data monitoring committee (DMC) will not be necessary

### Adverse event reporting and harms {22}

Patients will be invited to express any discomfort or inconvenience they may experience during the interventions; however, no adverse events are expected to be observed during the development and implementation of the different interventions planned in the trial.

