### Intervention description {11a}

Unified Protocol for the Transdiagnostic Treatment of Emotional Disorders (UP). The UP intervention will focus on a deficit in emotional regulation common to all emotional disorders (ED). Specifically, the intervention will address the adaptive value of emotions and promote tolerance to intense emotions as well as identify and modify dysfunctional emotional regulation strategies. Patients will receive 8 group therapy sessions (8–10 cancer survivors per group) with all UP modules [20]. The Spanish version of the therapist’s guide and the patient’s workbook will be used [21]. All patients will receive the workbook to inform them of the contents of each session, aid them in doing the recommended exercises between sessions, and help them once the treatment is completed. The treatment will last 8 weeks (one session per week) as follows:*Session 1: Motivation for change and commitment to treatment.* The main objectives of the first session are to establish the therapeutic relationship and promote motivation for change. Therefore, tasks pursuing that goal will be carried out such as the analysis of the advantages and disadvantages of change and the setting of treatment goals or life goals.*Session 2*: *Understanding emotions.* The second session will focus on teaching the adaptive components of emotions in patients and will begin by working with the concept of emotion-driven behaviors (EDBs), differentiating between three emotional components: behaviors, thoughts, and physical reactions.*Session 3: Emotional awareness training. Learning how to observe experiences.* In this session, patients will be trained in emotional awareness through the practice of exercises focusing on the present without judging what they are perceiving. For example, exercises involving mood induction with music.*Session 4: Cognitive restructuring.* The objective of this session is to promote cognitive flexibility. To achieve this aim, participants will be trained to identify and modify non-adaptive thoughts (e.g., through cognitive restructuring or positive self-instruction).*Session 5: Emotional avoidance and EDBs.* This session will analyze emotional avoidance patterns and EDBs as well as their role in the development and maintenance of emotional disorders. In addition, patients will be trained to modify their dysfunctional behaviors.*Session 6: Physical sensations tolerance.* In this session, the objective is to train patients in improving their tolerance to physical sensations. To this end, participants will learn to identify uncomfortable inner physical sensations associated with emotions using breathing exercises.*Session 7: Situational and interoceptive emotional exposure.* The objective of this session is to expose the patient to emotions by promoting habituation instead of emotional avoidance. A situational and emotional avoidance hierarchy will be developed and followed by exposure exercises for that purpose.*Session 8: Maintenance of treatment gains and relapse prevention.* In the last session, participants will check their progress and what was learned in previous sessions will be recapitulated to promote the later use of this knowledge once the intervention is over. The aim is to provide patients skills to deal with demanding situations in the future.

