Control group on waiting list. Once the interventions in groups 1 and 2 have been completed, the control group will receive the neuropsychological treatment described above. The group on the waiting list will participate in all the evaluations (T0, T1, and T2)

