### Provisions for post-trial care {30}

No potential harm is expected in this trial.

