#### Secondary outcomes

The secondary outcomes include changes in the level of QoL, anxiety, and depressive symptoms (QLQ C-30, BR23, and HADS) of the participants in both intervention groups, with better scores for the UP intervention group. Therefore, changes are expected in T1 with respect to T0 in the mean for QLQ C-30, BR23, and HADS scores and are expected to persist in T2. These scores are expected to remain stable in the waitlist group. The expected changes are manifested by a decrease in the score for each scale. Zwerenz et al. [24] used the HAD scale, specifically the depression subscale (HADD), to measure depressive symptoms and considered a variation of at least two points in the different measures as a clinically significant change in symptoms. Therefore, this study assumes that a variation of at least two points from the mean on the anxiety (HADA) and depression (HADD) subtests indicates a clinically significant change in symptom intensity. According to various authors, a change in QLQ C-30 scores of 5 to 10 can be considered as “little” change in terms of quality of life and of 10 to 20 as “moderate” change, while if this variation is greater than 20, the change is “very much” and a change of 10 points is considered meaningful [25, 26]. Thus, this study considers that a variation of 5–10 points, 10–20 points, and more than 20 points from the mean are considered as slight, moderate, and high significant changes, respectively.

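### Adverse events are invited only in connection with the interventions, so reports cannot be compared with the waitlist between T0 and T1 and have no explicit window up to T2

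*Protocol article*

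**What the plan says.** The section Adverse event reporting and harms {22} states a single method: "Patients will be invited to express any discomfort or inconvenience they may experience during the interventions". The same sentence adds that "no adverse events are expected to be observed during the development and implementation of the different interventions planned in the trial". The section on post-trial care {30} says "No potential harm is expected in this trial", and the section on the data monitoring committee {21a} gives as its reasons for not having one "the short duration of the interventions and no expected estimated risks for participants".

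On the waitlist arm, Intervention description {11a} says "The group on the waiting list will participate in all the evaluations (T0, T1, and T2". It also says that, once groups 1 and 2 have finished, "the control group will receive the neuropsychological treatment described above"; Trial design {8} describes this as an option that will be offered.

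The UP programme includes exposure work by design. Of session 7 the article says "The objective of this session is to expose the patient to emotions by promoting habituation instead of emotional avoidance".

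Under Secondary outcomes, HADS, QLQ-C30 and BR23 are compared across T0, T1 and T2. For HADS the article sets this criterion: "a variation of at least two points from the mean on the anxiety (HADA) and depression (HADD) subtests indicates a clinically significant change". The expected direction is a fall in scores.

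**The concern.** An adverse-event rate can be interpreted only if it is sought in the same way in each arm and over a known window. Here the invitation is tied to receiving an intervention. Breast cancer survivors have background distress whether treated or not. Discomfort reported in the UP or neuropsychological arm would have no waitlist rate to set against it, and a problem that first appears after the last session falls outside the wording.

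Some transient discomfort is foreseeable from the content of the UP sessions, and the expectation of no risk is one of the reasons given for having no monitoring committee. A report that no adverse events were seen would therefore depend partly on who was asked and about which weeks.

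**Working it through.** The plan gives no harms figure to reproduce. The check sets the harms wording against the visit schedule.

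**Inputs**
- 41 per arm, 123 in total (Sample size {14}).
- 8 weekly sessions in each active arm (Intervention description {11a}).
- T2 at 6 months after the intervention ends (Trial design {8}), taken as about 26 weeks.
- Internal consistency of HADS anxiety 0.85 (the HADS paragraph of {18a}).

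**1. Who is reached between T0 and T1.** The two active arms are in treatment and the waitlist is not. The share outside the invitation is 41/123 = 33.3%. This is also the only period sure to have an untreated comparator, because the waitlist may be treated after T1.

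**2. Which weeks are reached in the active arms.** 8/(8 + 26) = 23.5% of the time from start of treatment to T2.

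**3. Does the reading of the sentence matter?** The words on the interventions may limit when patients are asked, or which discomfort counts. On the first reading, asking stops when treatment stops. On the second, patients might report later, but only discomfort that arose in treatment. On both, an untreated waitlist participant has nothing to report under the rule, and a problem arising between T1 and T2 is not covered.

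**4. Do the rating scales close the gap?** In part. HADS, QLQ-C30 and BR23 are measured in all arms at all three times, and the mixed models estimate mean change in either direction. A mean improvement can still conceal a minority who worsen, and unwanted effects outside the items are not captured. Some patients who stop attending may also be missed: missing two or more appointments leads to exclusion {11b}, and the follow-up reminder calls are described for those who complete the sessions {18b}.

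**5. How far can a 2-point rise be read as harm?** Assume that 0.85 serves as reliability over time, that the standard deviation (not given in the article) is 3 to 5 points, and that errors are normal. For a patient with no true change, the standard deviation of the difference is SD × √(2 × (1 − 0.85)) = 0.548 × SD.
- SD 3: 0.548 × 3 = 1.64; 2/1.64 = 1.22; probability of a rise of 2 or more about 11%.
- SD 5: 0.548 × 5 = 2.74; 2/2.74 = 0.73; probability about 23%.

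So 11% to 23% of unchanged patients would cross the threshold on the anxiety subscale alone. Only the difference between arms carries information.

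**Context.** With no events in 41 participants, the one-sided 95% upper bound on the true rate is 1 − 0.05^(1/41) = 7.0%; for both active arms together it is 1 − 0.05^(1/82) = 3.6%. These bounds follow from arm size, assume that everyone was asked, and do not measure how much harm is missed.

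**The case against.** The strongest reply is that harm-relevant data do exist in every arm. A reader might infer from the harms section that the waitlist arm and the follow-up have no harm data at all. The documents do not support that: the three scales are collected in all arms to T2, and the waitlist would come under the invitation if later treated. A reader might also infer that worsening is ruled out of the HADS criterion. It is not: the 2-point variation is stated without direction, and the fall is only what is expected. What remains is that no by-arm count of individual worsening is stated.

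Two further inferences fail. The article does not say that discomfort is voiced to therapists in sessions; it names neither who asks nor where. And the absence of harm is an expectation, not an objective, hypothesis or planned conclusion, so the trial cannot be faulted for failing to prove it.

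It can also be said that a condensed article may leave adverse-event procedures to the full protocol. That stands for forms, grading and reporting routes. It does not dispose of the point, because this section states a method and a scope, and the scope is unequal between arms. Other routes are described, such as exclusion on relapse or a second cancer and yearly information to the ethics committee, for which recruitment and withdrawal numbers are named. None of these asks all arms about unwanted effects.

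**Conclusion.** The point holds as a limited one. As written, adverse-event reports cannot be compared with the waitlist between T0 and T1, where 41 of 123 participants (33%) lie outside the invitation. They also have no explicit window over the roughly 26 weeks to T2, so the treatment period covers about 24% of the time from start of treatment to T2. These figures describe who and when, not an amount of harm missed.

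The finding rests on the wording of the harms section as published and on 26 weeks for 6 months. It leaves the primary and secondary efficacy analyses untouched. It is worth correcting because the asymmetry is avoidable at visits that already take place.

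**What to change.** In Adverse event reporting and harms {22}, keep the present invitation and add two things.

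1. **One short open question on unwanted effects**, identical in all three arms, at T1 and T2. Participants complete it in writing after the outcome tests, and the blinded assessors do not see it. Report the answers by arm.
2. **A by-arm table from HADS data already planned**: the number of participants whose anxiety or depression subscale rises by at least 2 points. T0 to T1 is the comparison with an untreated control. T0 to T2 is descriptive, since the waitlist may have been treated by then. State that the article's 2-point criterion, worded as variation from the mean, is here applied to individual change, and that the table is read as a between-arm comparison, not as a list of harm events.

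The cost is one extra item at each of two existing visits and one table. Answers may reveal allocation if assessors see them, and a leak at T1 could affect assessment at T2; hence the separate written form. The question needs the amendment route described in {25}. The HADS table needs no new data and remains possible whatever the stage of recruitment.

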### Frequency and plans for auditing trial conduct {23}

This trial will be monitored by an independent committee of the Andalusian Biomedical Research Ethics Board. This committee requires annual information about the trial for its review, including the number of participants recruited and participants withdrawing. The members of the research group will meet once a week to evaluate the progress of the trial. The interventions of the different groups will be carried out by psychologists with at least a master’s degree in clinical psychology and with prior training in both the UP and the neuropsychological intervention before the start of the interventions. In addition, to address any concerns that may arise during the intervention period, the therapists in charge of carrying out the interventions will be supervised by a coordinator in scheduled coordination meetings.

### Plans for communicating important protocol amendments to relevant parties (e.g. trial participants, ethical committees) {25}

Any possible modification of the protocol during the trial, including changes in study design, sample size, or procedures, will require a modification of the protocol. These possible modifications to the protocol will be agreed upon by the research team, notified to the Andalusian Biomedical Research Ethics Committee and approved prior to their implementation.

### Dissemination plans {31a}

The results of the study will be disseminated at specialized scientific conferences and through publications in peer-reviewed indexed journals in the field of clinical psychology and psycho-oncology. The research team will decide on authorship and order of the authors depending on the contribution of each member.

## Discussion

Cancer patients frequently develop cognitive impairments that negatively affect their quality of life and functional status, especially those who have undergone chemotherapy [3–5]. Several psychological interventions to reduce the frequency of these cognitive alterations have shown positive results. However, a relationship has been observed between emotional well-being (anxiety and depression) and the severity of cognitive alterations in these patients. Therefore, a transdiagnostic intervention can be useful to improve their emotional state and cognitive performance [8–16].

This protocol includes information on a randomized controlled trial in which an intervention based on Barlow’s Unified Protocol (UP) will be carried out with the aim of improving the emotional state and cognitive performance of cancer patients. The UP intervention will be compared to a well-established neuropsychological intervention and a waiting list group. The group assigned to the transdiagnostic intervention group is expected to obtain significantly better outcomes in cognitive performance, anxiety, depression, and quality of life compared to the other two groups.

The planned trial has certain strengths that deserve mention. First, it will include a significant number of participants after estimating the sample size necessary to obtain relevant results. Furthermore, using a randomized controlled trial is an advantage of this protocol, as well as the inclusion of a waitlist control group with which to compare the results. Finally, the intervention based on the transdiagnostic model can help not only to improve the cognitive performance of the participants, but also their emotional state.

Finally, it is necessary to mention some limitations foreseen in this trial. The different treatments which the participants will undergo may influence the results. In addition, differences in the time from completion may influence the participants’ outcomes, although the effect of time on the results is expected to be controlled. Finally, the inclusion of patients with breast cancer only may limit the usefulness of the results, since cognitive alterations appear in cancer patients in general.

Despite these limitations, the expected results of this randomized and controlled trial can help to achieve a comprehensive improvement in cancer patients in relevant areas such as cognitive function and emotional state.

## Trial status

Protocol version v01. 12 March 2022. This trial is currently ongoing, with activity and recruitment beginning on April 25, 2022. Recruitment completion is expected on August 31, 2022

## Data Availability

Only the members of the research team will have access to study data.
